**Background:**

Cardiovascular diseases (CVDs) are the leading cause of mortality globally, claiming over 17 million lives annually. Notably, low- and middle-income countries (LMICs; i.e., based on World Bank classification) have experienced a disconcerting surge in CVD deaths over the past two decades, with more than 80% of world's CVD deaths concentrated in these countries. Projections indicate that CVD is poised to remain the single leading causes of death by 2030. While advancements in medical technology and treatment have led to a decline in CVD mortality rates in high-income countries, the prevalence and incidence remain high. Consequently, the number of individuals grappling with chronic CVDs and associated disabilities is on the rise, contributing to 10% of the global burden of disease. CVD is also on the rise as a significant health burden in developing nations, with particular concern related to the comparatively early onset of CVD-related deaths in LMICs in contrast to developed countries, resulting in more pronounced negative impacts on economic productivity and the labor force.

Indeed, the economic impact of CVD on health systems is substantial, encompassing both direct and indirect costs such as expenses related to healthcare services, medications, and lost productivity due to mortality and morbidity. CVD costs the European Union €\$210 billion a year, and the American economy US\$407.3 billion in 2019.

Cardiac Rehabilitation

Cardiac Rehabilitation (CR) is a comprehensive outpatient secondary prevention model of care which mitigates this health and economic burden. CR programs deliver individualized, inter-professional care, including: medical assessment, structured exercise training, patient and family education, cardiovascular risk factor management (e.g., optimization of medications to control

lipids, hypertension, tobacco use) and psychosocial counselling. Patients generally come to a clinical centre for 1 hour-long sessions per week over several months. Patients are very satisfied with CR care.

The many clinical benefits of CR are supported by rigorous meta-analyses randomized controlled trials. It is internationally-agreed that CR participation enhances quality of life in a clinically meaningful way, and lowers morbidity and mortality by approximately 25%. CR improves return to work and reduces downstream healthcare utilization, at very low cost. For these reasons, clinical practice guidelines around the world recommend CR referral for CVD patients.

### Evidence-practice gaps

Despite these benefits, unfortunately CR is grossly under-used around the world. When compared to other clinical guideline recommendations for CVD inpatients and outpatients, CR referral is the least well-implemented. Data from the United States (US) shows <30% of CR-indicated patients enrol. Data shows that if every CR program in the US was filled to capacity plus 10%, still only 45% of CR-indicated patients could be served. Except Sweden and the United Kingdom, access rates are also abysmal in the only other countries where data are available, such as Australia, Europe, Japan, and South Korea. Many countries experiencing a demographic transition from communicable to non-communicable diseases are establishing cardiology services with expensive diagnostic and treatment technologies, but neglecting CR despite the Guidelines. In sum, unfortunately CR access is inequitable, with socio-economically disadvantaged patients having even less access, and other vulnerable patients such as those living in rural areas, women, and ethnocultural minorities.

Reasons for CR under-utilization are well-established, with factors from the patient to health system level at play. The major issue is lack of available programs to serve patients. Indeed, the International Council of Cardiovascular Prevention and Rehabilitation (ICCPR; PIs on Executive) – an umbrella organization of CR Societies globally- conducted a first Global Audit of CR programs in 2016/2017 which was the first ever to quantify program availability. Of 203 countries recognized by the World Health Organization (WHO), it was established for the first time that only 111 (55%) had any CR; only 17% of countries in Africa have any CR. Annual patient capacity in each program was ascertained and juxtaposed against ischemic heart disease estimate in every country of the world from the Global Burden of Disease (GBD) study revealing only one CR “spot” for every 12 new patients in need each year. Indeed, when summarizing across the globe, countries had a median of only 4 programs, and had capacity to serve a median of only 120 patients per year. Globally, 16.3 million more CR “spots” are needed each year to treat incident ischemic heart disease (IHD) patients, with 14 million of those spots needed in LMIC. For instance, India and China each need over 3 million more spots per year, with Russia 1.2.

ICCPR utilized the results from this first Audit to advocate for increases in CR capacity, with unmet CR need data for each country disseminated widely through national champions. In addition, resources to support development of quality programs, particularly in resource-poor settings, were created.

In response to calls from ICCPR members based on reports of massive program closures due to the COVID-19 pandemic, the Audit was repeated in Spring 2020. Disconcertingly, results revealed three-quarters of programs had stopped CR delivery, which would correspond to ~4500 programs affected. For infection prevention and control, many operational programs quickly transitioned to unsupervised delivery, primarily through low-tech modalities such as phones. Hybrid CR is defined as offering patients both on-site and remote/unsupervised delivery. Home-based or unsupervised CR +/- technology allows individuals to engage in CR activities from the comfort of their homes. Unsupervised CR typically involves virtual consultations, the use of online education resources, and technology for exercise monitoring. However, such remote CR was scantily reimbursed by government or insurance companies, raising questions of sustainability and patient access.

## **Study Objectives**

The overall objectives of this mixed-method study are to: (a) update the status of CR availability and capacity around the globe, as well as CR service indicators (shortfall/surplus [n] and coverage [% and rank]), (b) investigate CR delivery mode changes since the pandemic (supervised to unsupervised/hybrid), and (c) understand as well as improve CR access and equity.

## **METHODS**

### **Study Design**

This is a mixed-method study, using an exploratory sequential design. It comprises a cross-sectional Audit with program survey in the first stage. These results will be used to inform the second stage qualitative interviews (please note: degree of breadth to be based on resource availability). The methods will be integrated by means of merging, such that results of both stages will be brought together for analysis contiguously. This will be used to inform knowledge translation (KT).

### **Procedure**

#### Quantitative:

OBJ 1: Using WHO's list of countries, the initial step of confirming countries with available CR services will involve review of results from the first CR Global Audit and the 2020 CR Audit (i.e., during the pandemic). Verification of CR availability will be undertaken for countries believed to have no CR at that time of the previous Audit or <10 programs.

First, the investigative team will approach contacts for these countries from the previous Audits for information, and where verification is not possible they will: (a) thoroughly search via Google using the term “cardiac rehabilitation” and “name of country”, (b) searching via Google for academic hospitals within these countries, whose websites will then be searched for CR programs, (c) consulting through the ICCPR network for contacts with any other local CR experts, (d) attendance at international conferences organized by CR-related Societies to engage with experts from the respective countries, and (e) seeking contacts and information from other CR-related international organizations (e.g., International Society of Physical and Rehabilitation Medicine [ISPRM]) before any country is designated as having no CR.

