## **Measures**

*Quantitative:*

*Objective 1:*

Countries will be characterized by World Bank income class (i.e., 4) and WHO region (i.e., 6). Surveys without country specified were grouped together separately but maintained in the sample to promote generalizability. The indicators below will be aggregated at the country, region, income class and global analytic levels.

CR need: raw IHD incidence per country from latest Global Burden of Disease estimates (2023; <https://vizhub.healthdata.org/gbd-results?params=gbd-api-2021-permalink/6afc006e91ec18286cf82cec24bc38c1>), minus correction value as described below.

To conservatively take into account that some patients do not survive an incident event (e.g., 30-day survival) to the point of initiating CR or they suffer comorbidities which render them ineligible for CR (inability to ambulate, comorbid terminal condition, comorbid sensory or cognitive impairment), a correction was applied to national incidence values to represent a more true CR-eligible population estimate. Based on the literature showing inequality in CVD morbidity and mortality, we assumed that 85% of incident IHD patients in HICs would be eligible for CR, 80% in MICs, and 75% in LICs.

CR availability: existence of  $\geq 1$  program in a country (yes/no), with the total number of available programs ascertained by the national champions.

CR capacity refers to the number of patients a program reports they could serve annually. For each program, total capacity was computed as the sum of annual supervised and unsupervised capacity. For programs that offered either CR model but had missing or outlier (i.e.,  $>10,000$ ) capacity values, the median capacity for the WHO region of the country in which program is located was imputed. However, while not applicable for supervised models given number of responses, if  $<5$  programs within a region reported capacity for unsupervised CR, the overall median unsupervised program capacity across all MICs was applied (i.e., 75), as none of the remaining countries with missing data were classified as HICs and only 2 responding countries were LICs. Zero capacity reflects no availability.

Median program capacity was determined based on the total capacity values across all programs within that country. This was then multiplied by the number of programs in the country to ascertain national CR capacity.

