## **Data Analyses**

### Quantitative:

#### Objective 1 (GBD):

Current CR availability and capacity will be characterized descriptively at all analytic levels.

Changes in CR availability (i.e., none versus now have any) from the initial Audit at the country level will be quantified. The rapid COVID Audit did not focus on capacity indicators other than program closure due to the pandemic, and hence change from that Audit were not considered. Change from 2016 to present in percent of countries in each income class and region with any CR availability will be described.

CR capacity was a sum of supervised and unsupervised program capacity; only supervised capacity was considered in the initial Audit. Therefore, capacity changes will only be examined descriptively; for changes, the IHD only data will be used, and inferential tests will not be performed given the improved approach in capturing the indicated sample.

CR service levels and coverage will be computed as outlined above at all analytic levels. Coverage values will be ranked by country.

CR service shortfall/surplus and coverage values incorporate GBD incidence estimates. Their CR-indicated condition category changed from the initial Audit (ACS only to now IHD including also angina and ischemic-caused HF). Given also changes in the capacity measure (inclusion in current Audit of unsupervised capacity, these indicators will be juxtaposed by country descriptively from the first Audit estimates and change computed. Change from the first Audit by income class and region will be described, without inferential tests as above.

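### Change in availability since the first Audit is defined without asking when a newly found program opened, so a country missed at baseline would be counted as a gain

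*Protocol*

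**What the plan says.** In the Protocol, Procedure, Quantitative (OBJ 1), the current Audit begins by reviewing the first Audit and the 2020 Audit. It then re-checks a subset of countries: "Verification of CR availability will be undertaken for countries believed to have no CR at that time of the previous Audit or <10 programs". The order of the re-check is stated: "First, the investigative team will approach contacts for these countries from the previous Audits for information, and where verification is not possible they will" use routes (a) to (e), namely web searches, academic hospital websites, the network of the international council, conferences and other international organizations. All of this comes "before any country is designated as having no CR".

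Measures, Objective 1, defines availability as one or more programs existing in the country, "with the total number of available programs ascertained by the national champions". The definition has no condition on when a program began.

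Data Analyses, Objective 1 (GBD), sets the change measure: "Changes in CR availability (i.e., none versus now have any) from the initial Audit at the country level will be quantified". It adds: "Change from 2016 to present in percent of countries in each income class and region with any CR availability will be described". The same section sets the 2020 Audit aside for change.

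The baseline is in Background, Evidence-practice gaps: "Of 203 countries recognized by the World Health Organization (WHO"), "it was established for the first time that only 111 (55%) had any CR".

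**The concern.** The country's 2016 status is taken as recorded, while its current status comes from a new round of enquiry in countries that include those recorded as having none. Any repeat enquiry can find something an earlier one missed. Under the stated rule, a country with a program that has run since before 2016 moves from none to any in the same way as a country whose first program opened in 2022. The reader of the result cannot separate the two.

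The plan handles this kind of problem elsewhere. Data Analyses, Objective 1, warns that capacity is not comparable with the first Audit because unsupervised delivery is now included, and that need and coverage are not comparable because the indicated condition widened. It restricts those comparisons to description for that reason. The availability change carries no such caution.

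At stake is the Objective 1 statement of how many countries have gained CR since 2016, overall and by region and income class. Knowledge Translation says that Societies will receive country-specific summaries for advocacy. A false gain would credit progress that did not occur and hide provision that was already there. Estimates of current availability are not affected.

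**Working it through.** **Inputs from the protocol.** Countries in the first Audit: 203. Countries with any CR: 111, stated as 55%. Regions: 6 (WHO). Income classes: 4 (World Bank). The number of countries wrongly recorded as having none is not given and is varied below as an assumption. The denominator is taken as 203 at both times, also an assumption.

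**Step 1: reproduce the baseline.** 111/203 = 54.7%, which rounds to the stated 55%. Countries recorded as none: 203 − 111 = 92.

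**Step 2: how the rule treats a missed country.** Let A0 and A1 be the true numbers of countries with CR in 2016 and now, and M0 and M1 the numbers with CR that each Audit failed to find. Assume that neither Audit records CR where there is none.

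- Recorded change = (A1 − M1) − (A0 − M0) = (A1 − A0) + (M0 − M1).
- Bias in the net change = M0 − M1, so programs missed now pull the net figure down and countries missed at both times cancel.
- In the country-level list of gains, every country missed then and found now is a false gain, whatever M1 is.

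**Step 3: size per country.** Global: 1/203 = 0.49 percentage points. Within a group of n countries: 100/n points. Average region: 203/6 = 33.8 countries, so 100/33.8 = 3.0 points. Average income class: 203/4 = 50.75 countries, so 100/50.75 = 2.0 points. Actual groups differ in size; a group of 45 (assumed) gives 100/45 = 2.2 points.

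**Step 4: range under assumed shares.** Let m be the share of the 92 that had CR in 2016 and are found now, with k = 92 × m rounded. False gain = 100 × k/203. Restated baseline = 100 × (111 + k)/203.

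| m (assumed) | k | False gain (points) | Restated 2016 figure |
|---|---|---|---|
| 2% | 2 | 1.0 | 55.7% |
| 5% | 5 | 2.5 | 57.1% |
| 10% | 9 | 4.4 | 59.1% |
| 20% | 18 | 8.9 | 63.5% |
| 30% | 28 | 13.8 | 68.5% |

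**Step 5: effect on a headline figure.** Suppose 20 countries move from none to any (assumed) and 5 of them already had CR. The reported gain is 20/203 = 9.9 points, the true gain is 15/203 = 7.4 points, and 5/20 = 25% of the reported gain is false.

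**Step 6: is a date collected anywhere?** The survey domains listed under Measures, Objectives 1-3, do not name an opening year. The questionnaire itself is not shown, so an item may exist. Even if it does, the change definition does not use it.

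**The case against.** The strongest reply is that nothing shows the first Audit missed any country. Its search method is not described in the protocol and may have been the same as the present one. This stands. A reader might infer that the current search is more intensive and that reported growth will be largely better detection; the protocol does not support that, and the size of the bias is unknown.

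A reader might also infer that every country recorded as none is searched by all five routes. The text makes those routes a fallback for when contacts from the previous Audits cannot settle the matter. Nor does the plan count each program found as new: the unit is the country and its status.

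A third tempting reading is that the error in the reported change can only run toward growth. The re-check also covers countries with fewer than 10 programs, where a fall to zero could be found, and programs missed now lower the net figure (the M1 term). So the net change could be biased either way. But an offset in the total does not turn a false gain into a true one, and the plan quantifies gains by country.

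It is also tempting to say that the distortion is worst where availability was lowest, since only 17% of African countries had any CR. More countries there are exposed to the error, but the protocol does not show that more were missed.

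Finally, the comparison is descriptive, and a sensitivity analysis could sit in a SAP that is not at hand. The analysis split could. The opening year, however, has to be obtained from contacts and cannot be created at the analysis stage, and the change rule itself is fixed in the protocol.

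**Conclusion.** The point holds as a limit of the change definition, not as a demonstrated error in the results. Followed exactly, the plan counts a country as a gain when its program was running in 2016 and was simply not found, because availability is undated and the 2016 status is never restated. Up to 92 of 203 countries are exposed. Each one affected adds 0.49 points globally, and about 3.0 points in a region or 2.0 in an income class of average size. Totals such as 2.5 points for 5 countries or 8.9 points for 18 rest entirely on assumed counts. The size and the net direction of the bias cannot be determined from the protocol. The change is worth making because the remedy is cheap and the plan already takes care over comparability for its other indicators.

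**What to change.** Add a collection step to Procedure, Quantitative (OBJ 1). For each country moving from none to any, ask the contact, champion or program for the year in which its earliest eligible program opened, using the current inclusion criteria.

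In Data Analyses, Objective 1 (GBD):

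- Class each such country as newly opened (after the first Audit's data collection), newly detected (already operating then) or unknown.
- Report the three groups separately, overall and by region and income class.
- Give the change since 2016 with newly detected countries moved into the baseline, alongside the unadjusted change.
- Describe the unadjusted figure as change in detected availability.

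If data collection has closed, the same question can be sent to the contacts for the newly positive countries alone. Failing that, the relabelling can still be made.

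The cost is one extra question for a limited set of countries. The downsides are a possibly smaller growth figure, reliance on recall of opening dates and past eligibility, and some unknown years. The fix corrects false gains only; it does not re-check countries recorded as having CR in 2016, and the report should say so.

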#### Program Identification:

An MS Excel spreadsheet of all countries in the world which offer CR will be generated. Upon identifying countries offering CR, in the countries believed to have at least several programs, an “Audit champion” will be sought. First, we will contact the leadership of the ~50 available CR-related Society through ICCPR’s network requesting a Board member or other appropriate party to serve as champion. In cases where no Society is available, Ministries of Health and international organizations (e.g., ISPRM) will be contacted. If no support can be secured, champions from the previous Audit will be invited.

They will be emailed requesting collaboration in the study in return for potential authorship and provision of country-specific information on CR. Agreeing champions will be asked to circulate the email to participants with the survey link, or to provide us with CR program emails to contact directly ourselves.

#### Program Survey (OBJ 1-3):

The most responsible clinician of the identified CR programs will be sent an e-mail requesting her/his participation and a link to the survey.

Informed consent will be sought through an online consent form. Respondents will be required to click a box to consent and proceed to complete the survey. The survey will also be administered through a web-based program (REDCap).

Non-respondents will be sent a follow-up e-mail reminder 2 weeks later. Respondents will be provided free access to ICCPR’s clinician training if they elect to receive it, by providing their email at the end of the survey (no other identifying information).

#### Qualitative (OBJ 3):

Interviews will be held with participants from three stakeholder groups to understand strategies and enablers to CR capacity increases. Champions will be enlisted to approach potential interviewees in specific countries via email and phone. Clinicians volunteering for interview at

the end of the survey will be considered. Through ICCPR also, representatives from Societies in the countries with greatest need will be approached.

Those willing will be extended invitations to participate in one-hour, one-on-one semi-structured interviews via Zoom. After training and piloting, interviews will be conducted by the PhD student; They will not be known to the interviewees. A second team member may be present to record non-verbals, and emotion expressed.

Given English may not be the first language for some interviewees, all interviewees will be provided the questions in advance, they will be shared on screen through the interview, the interviewers will ensure their cameras are on so their faces are visible, and live auto-transcript will be enabled.

Interviews will be digitally audio-recorded. Auto-transcripts will be cleaned verbatim while ensuring anonymity before audio-recording destruction.

